# Outcome of patients after lower limb fracture with partial weight bearing postoperatively treated with or without anti-gravity treadmill (alter G®) during six weeks of rehabilitation – a protocol of a prospective randomized trial

**DOI:** 10.1186/s12891-017-1461-0

**Published:** 2017-03-14

## Abstract

**Background:**

Partial or complete immobilization leads to different adjustment processes like higher risk of muscle atrophy or a decrease of general performance. The present study is designed to prove efficacy of the anti-gravity treadmill (alter G®) compared to a standard rehabilitation protocol in patients with tibial plateau (group 1)or ankle fractures (group 2) with six weeks of partial weight bearing of 20 kg.

**Methods and Design:**

This prospective randomized study will include a total of 60 patients for each group according to predefined inclusion and exclusion criteria. 1:1 randomization will be performed centrally via fax supported by the Clinical Trial Centre Leipzig (ZKS Leipzig). Patients in the treatment arm will be treated with an anti-gravity treadmill (alter G®) instead of physiotherapy. The protocol is designed parallel to standard physiotherapy with a frequency of two to three times of training with the treadmill per week with duration of 20 min for six weeks.

**Discussion:**

Up to date no published randomized controlled trial with an anti-gravity treadmill is available. The findings of this study can help to modify rehabilitation of patients with partial weight bearing due to their injury or postoperative protocol. It will deliver interesting results if an anti-gravity treadmill is useful in rehabilitation in those patients. Further ongoing studies will identify different indications for an anti-gravity treadmill. Thus, in connection with those studies, a more valid statement regarding safety and efficacy is possible.

**Trial registration:**

NCT02790229 registered on May 29, 2016

## Background

Partial or complete immobilization leads to different adjustment processes like muscle wasting or a decrease of general performance. The degeneration of the immobilized muscle groups and early joint stiffness are essential factors causing a prolonged course of healing [1–4].

An injury with subsequent time of immobilization is a challenge for patients to regain muscle mass and function. Despite animal studies proving that immobilization causes muscle atrophy, until now, it has not been possible to counteract muscle degeneration during immobilization.

To date, only several case reports or small case series dealing with rehabilitation with an anti-gravity treadmill exist. Most of them are cases with individual treatment of one patient [5–7].

Saxena et al. compared patients treated with or without anti-gravity treadmill after surgery for Achilles tendon tears. They included eight patients per group and found no difference between the groups [8].

Two studies by Webber and Hoffman in elderly and young patients showed an improvement of their oxygen exchange with decrease of heart and breathing rate during training in an anti-gravity treadmill. Thus it was possible to perform higher intensity training [9, 10].

A recent study by Peeler et al. used an anti-gravity treadmill for pain reduction and muscle training in patients with knee arthrosis. They were able to prove that an anti-gravity treadmill is easy to use and they could demonstrate with their patients an increase in muscle strength and joint function plus a pain decrease [11].

Cutuk et al. demonstrated no negative effect to blood pressure or heart rate independently of the pressure in the anti-gravity treadmill. Thus they concluded that patients with hypertension or higher cardiovascular risks can be treated with an anti-gravity treadmill. Moreover they showed a positive effect on range of motion of the knee and ankle [12].

Summarizing previous studies demonstrated safety and, to a limited degree, efficacy of treatment with an anti-gravity treadmill during rehabilitation. To our knowledge no prospective randomized study is available in order to prove efficacy of an anti-gravity treadmill compared to a standard rehabilitation protocol.

### Aim of this study

The presented study is designed to prove efficacy of the anti-gravity treadmill (alter G®, Fig. 1) compared to a standard rehabilitation protocol in patients with tibial plateau or ankle fractures with six weeks of partial weight bearing in regard to both subjective and objective variables at predefined times as described under “outcome measures”.

**Fig. 1 Fig1:**
[figure not shown]
Anti-gravity treadmill (alter G®)

## Methods/Design

### Recruiting hospitals

Two hospitals recruit patients for the study. Both hospitals are national trauma centers. Retrospective data analysis showed that between 80 and 100 patients with ankle or proximal tibia fractures are treated per year in each hospital.

### Participants

The study will include 60 patients per group, both men and non-pregnant women with postoperative partial weight bearing of 20 kg after tibial plateau (group 1) or ankle fracture (group 2). It will include patients aged 18 to 65 years old.

### Inclusion and exclusion criteria

All patients will be assessed clinically preoperatively prior to inclusion to avoid subsequent exclusion. The definitive inclusion will be done after surgery and assignment to partial weight bearing of 20 kg for six weeks. Exclusion criteria are patients with more than 100 kg body weight, restriction of range of motion due to fracture morphology, serious illness or poor general health as judged by a physician that may influence the rehabilitation, open fractures (>1° according to Gustilo and Anderson) or surgical site infection which would cause a longer hospital stay, pregnancy, neuromuscular disorders, or preexisting muscle atrophy. Patients declining participation in the trial (and who fulfill the inclusion criteria) or withdrawing during the study will receive appropriate treatment according to the standard of care.

### Randomization

Randomization will be performed for each group centrally via fax supported by the Clinical Trial Centre Leipzig (ZKS Leipzig). Allocation to the experimental arm (randomization ratio 1:1) uses block randomization with variable block lengths (Fig. 2). Randomization will not be stratified.

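### Randomisation is not stratified by hospital although two hospitals recruit and allocation is central; chance imbalance and a small loss of precision could be avoided, and the wording should be clarified (minor)

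*Protocol article*

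**What the plan says.** The Randomization section of the protocol article opens with "Randomization will be performed for each group centrally via fax", states that allocation "uses block randomization with variable block lengths" in a 1:1 ratio, and closes with "Randomization will not be stratified".

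The Participants section defines the groups by fracture: "after tibial plateau (group 1) or ankle fracture (group 2"). The same section gives the size: "The study will include 60 patients per group". The Sample size section expects 50 of the 60 to be analysed in each fracture group.

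Under Recruiting hospitals: "Two hospitals recruit patients for the study". That section also gives their volume: "between 80 and 100 patients with ankle or proximal tibia fractures are treated per year in each hospital".

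The Statistical analysis section bases power on a two-sided t-test within each fracture group, with 25 per arm, SD 18 and a difference of 15 points. It mentions no hospital term.

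**The concern.** Two things in the Randomization section draw attention.

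The first is wording. Separate lists for each fracture type are a form of stratification, so the opening and closing sentences do not fit together if both are taken literally. A reader has to work out that the closing sentence means no factor beyond fracture type.

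The second is substance. Taken that way, the closing sentence rules out hospital as a factor. Patients are operated on before inclusion is final (Inclusion and exclusion criteria), and the control arm receives therapist-delivered physiotherapy (Rehabilitation protocol). Outcomes could therefore plausibly differ between hospitals, although the article gives no figure for this. Blocks that run over a whole fracture group balance the arms in total but not within a hospital. In a group of 60, one arm can by chance hold clearly more patients from one hospital. If the comparison is not adjusted for hospital, part of any hospital difference then appears in that trial's arm difference, and the rest adds to the residual variance. A central service already runs the allocation, so hospital could be added without extra patients.

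**Working it through.** **Inputs from the protocol article.** 60 randomised and 50 analysed per fracture group (30 and 25 per arm); SD 18; target difference 15 points; minimally important change 8-10 points; two-sided alpha 0.05; two hospitals of similar volume.

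**Assumptions, because the article gives no value.** Hospitals recruit equally; blocks of 4 and 6; hospitals differ by 5 to 10 points on the outcome.

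**1. The plan's own power.** Noncentral t, 25 per arm, 48 degrees of freedom:
- Standard error of the arm difference = 18 × √(2/25) = 5.09 points.
- Noncentrality for 15 points = 15/5.09 = 2.95, giving two-sided power 82.3% (stated 82%).
- For 10 points: 48.6% (stated 48%).
- One-sided: 89.6% and 61.5% (stated 89% and 61%).

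The stated figures reproduce and do not depend on how hospital is handled.

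**2. Chance of hospital imbalance in one fracture group.** Suppose exactly 30 of 60 patients come from each hospital and 30 go to each arm. The number from hospital A in the treadmill arm is then hypergeometric (60, 30, 30) with mean 15. A gap of 20 percentage points in hospital share means 18 of 30 (60%) against 12 of 30 (40%):
- P(|x − 15| ≥ 3) = 0.196.
- In at least one of the two fracture groups: 1 − (1 − 0.196)² = 0.354.

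This ignores blocking and fixes the hospital totals. A simulation of 40,000 lists per scenario, with blocks of 4 and 6 and the hospital totals free to vary, gives:

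| Patients | Hospital split | P(gap ≥ 20 points) | P(gap ≥ 30 points) | 95th percentile of gap |
|---|---|---|---|---|
| 60 | 50:50 | 14.5% | 2.6% | 27 points |
| 50 | 50:50 | 19.2% | 3.3% | 28 points |
| 60 | 30:70 | 11.1% | 1.4% | 23 points |

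With equal recruitment, the chance of a gap of 20 points or more is therefore about 15-20% per fracture group.

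**3. Effect on the arm difference.** Shift = gap in hospital share × hospital difference:
- Gap 0.20: 0.20 × 5 = 1 point; 0.20 × 10 = 2 points.
- 95th percentile, 60 patients, 50:50 (0.266): 0.266 × 5 = 1.3 points; 0.266 × 10 = 2.7 points.
- In standard errors, 1/5.09 = 0.2 and 2/5.09 = 0.4.

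**4. Precision gained by the fix.** If SD 18 includes a hospital difference g at a 50:50 split, the within-hospital SD is √(18² − g²/4):
- g = 5: √(324 − 6.25) = 17.8; power for 15 points 83.0%.
- g = 10: √(324 − 25) = 17.3; power for 15 points 85.2%.

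The comparison value is 82.3%. Using 47 instead of 48 degrees of freedom for the hospital term leaves both results unchanged to the first decimal. The number of patients stays the same.

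**The case against.** The case for leaving the design alone is strong in several respects.

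- **Validity.** Central block allocation does not depend on hospital. The comparison is unbiased on average and the unadjusted test keeps its type I error. Chance imbalance is ordinary sampling error, which the standard error covers provided SD 18 reflects patients from both hospitals. This stands. A reader might infer that arm is confounded with hospital; the documents do not support that.
- **Wording.** With group defined as fracture type, the section reads naturally as lists per fracture group and no further factor. The flow chart in Fig. 2, which is not shown in the text available, may make this explicit. This stands. A reader might infer that one list serves all 120 patients, with unequal arms inside a fracture group, but that sets aside the opening sentence of the section.
- **Size.** The 1-2 point shift needs both an uncommon split and an assumed hospital difference, and it is small against the 15-point target and the 8-10 point minimally important change. The treadmill programme is fixed and physiotherapy follows a standardised protocol, which should limit hospital differences. This stands and sets the severity.
- **Analysis model.** The article names the t-test in its power statement and does not exclude covariates. A hospital term may be in an analysis plan that is not shown. This stands, so the lack of a hospital term in the article is not in itself a defect.
- **Cost.** A reader might infer that omitting hospital brings no benefit. It does bring one: staff can see who uses the treadmill, and with a list per hospital they see every earlier allocation on their own list, so the end of a block is easier to guess. This stands, but variable block lengths limit it and covariate adjustment alone avoids it.

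None of this gives a reason for leaving hospital out of both the randomisation and the analysis.

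**Conclusion.** The point holds as a minor one. The article expressly rules out stratification beyond fracture group, so the two hospitals are not balanced between arms by design. The trial remains valid: there is no bias on average, no inflation of the type I error and no error in the stated power. What is given up is protection against chance imbalance (about 15-20% per fracture group for a gap of 20 percentage points or more, with equal recruitment) and a little precision (82% against about 83-85% power for 15 points). The shift of 1-2 points and the power gain both rest on an assumed hospital difference of 5-10 points. If the hospitals do not differ, there is neither shift nor gain. The two sentences on stratification are a matter of unclear wording with one natural reading.

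**What to change.** Reword the Randomization section to say that each fracture group has its own 1:1 lists with variable block lengths, stratified by hospital, at the same central service. That makes four lists in place of two. Include hospital as a covariate in the primary comparison within each fracture group, if the analysis plan does not already do so.

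If enrolment has begun, keep the existing lists, clarify that they are separate by fracture group with no further factor, and make only the covariate adjustment.

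The cost is two further lists, one degree of freedom per model and slightly greater predictability of allocation at each hospital, because the treatment given is visible to staff. No extra patients are needed. If predictability is the greater worry, the covariate alone on the present lists recovers most of the benefit.

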**Fig. 2 Fig2:**
[figure not shown]
Flow-chart of randomization and study groups

### Intervention

Treatment of patients with partial body weight bearing of 20 kg after surgery for a tibial plateau fracture (group1) or ankle fracture (group 2) with an anti-gravity treadmill (alter G®) instead of physiotherapy.

## Outcome measures

### Demographics

Demographics to be collected at inclusion include age, gender, height (cm), weight (kg), body mass index (BMI), injury mechanism, previous medical history, current medication, smoking or drug/alcohol abuse, social status, work status and health insurance.

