### Statistical analysis

Demographic and clinical characteristics will be presented as means and standard deviations (SD) or frequencies and percentages, as appropriate. The normality of continuous data will be assessed by examining the histograms. If necessary, a suitable transformation will be considered to symmetrize the data.

Our primary efficacy endpoint for tibial plateau fractures/ankle fractures is change from baseline (first day postoperative) to 12 months in overall KOOS/FOAS. Literature data suggest a standard deviation of about 18 in KOOS4/FOAS. We expect a similar standard deviation for overall KOOS/FOAS. The developer of the KOOS/FOAS reports a minimally important change of 8–10 points.

We want to power this study to detect a moderate effect of 15 points using a two-sided *t*-test with a significance level of 0.05. With 25 patients per arm per group, we will have a power of 82% to detect a difference between groups of 15 points (48% power for a difference of 10). Using a one-sided *t*-test, the power figures are 89% (resp. 61%).

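### The only test named for the primary endpoint is an unadjusted t-test, with unstratified allocation and no listed fracture class; this gives up precision and leaves small arms open to chance imbalance

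*Protocol article*

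**What the plan says.** - **Allocation.** Under Randomization, the article states "Randomization will be performed for each group centrally via fax" and "Allocation to the experimental arm (randomization ratio 1:1) uses block randomization with variable block lengths". Tibial plateau and ankle fractures are therefore allocated separately. Within each of them, "Randomization will not be stratified".
- **Baseline data.** Under Demographics: "Demographics to be collected at inclusion include age, gender, height (cm), weight (kg), body mass index (BMI), injury mechanism, previous medical history", followed by "current medication, smoking or drug/alcohol abuse, social status, work status and health insurance". Injury mechanism is listed; fracture class is not.
- **Reporting.** Under Statistical analysis: "Demographic and clinical characteristics will be presented as means and standard deviations (SD) or frequencies and percentages, as appropriate". The clinical characteristics are not itemised.
- **Test.** The same section says "We want to power this study to detect a moderate effect of 15 points using a two-sided" t-test at the 0.05 level. No covariate is named, and no other between-arm test is given for the primary endpoint.
- **Eligibility.** Inclusion and exclusion criteria remove open fractures above grade 1 and patients with "restriction of range of motion due to fracture morphology". Definitive inclusion follows surgery.

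**The concern.** Each fracture group is compared on 30 allocated and about 25 analysed patients per arm. At that size a baseline factor can easily fall unevenly between arms. If fracture severity affects function at 12 months, which is plausible but not stated in the article, an uneven split moves the estimated difference, and neither the allocation nor the named test takes account of it. Age is collected but has no role in the named test either.

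What is at stake is precision and the credibility of the estimate. The article cites a minimally important change of 8–10 points, yet by its own figure the power at 10 points is only about one half. Any variance that a cheap baseline variable could explain is worth having.

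**Working it through.** **Inputs from the article.** 60 patients allocated per fracture group at 1:1, so 30 per arm; 25 per arm analysed; SD 18; two-sided alpha 0.05; target difference 15 points, with 10 points also considered.

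**Inputs assumed, because the article gives none.** Share of severe fractures 30–50%; 12-month gap between severe and less severe fractures 5–20 points; share of variance explained by the covariates (R²) 2–30%.

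**1. The stated power.** The standard error of the arm difference is 18 × √(2/25) = 5.09. Noncentral t with 48 degrees of freedom gives 82.3% at 15 points and 48.6% at 10 points. The article says 82% and 48%, so its figures reproduce.

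**2. Chance of imbalance.** Consider arms that differ by at least 20 percentage points in the severe share.
- Two independent binomials, severe share 30–50%: 12–16% with 30 per arm, 16–20% with 25 per arm.
- Fixed number severe among 60, 30 per arm (hypergeometric): 11.0% at 23 severe, 18.7% at 24, 11.5% at 25, 19.6% at 30. It jumps because an odd total cannot produce a difference of exactly 20 points. At 24 severe, the chance of strictly exceeding 20 points is 6.4%. At 19 or 21 severe it is 9–10%.

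A fair summary is about 11–20% per group. With two independent groups, the chance that at least one is affected is 1 − 0.89² = 21% to 1 − 0.80² = 36%.

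**3. Shift in the estimate.** Shift = imbalance × prognostic gap.

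| Gap (points) | Shift at 20 percentage points | Shift / 5.09 |
|---|---|---|
| 5 | 1 | 0.2 |
| 10 | 2 | 0.4 |
| 15 | 3 | 0.6 |
| 20 | 4 | 0.8 |

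**4. Type I error of the unadjusted test.** Simulation (100,000 runs, 25 per arm, 40% severe) gives 5.0% for a 10-point gap and 5.1% for a 15-point gap. Conditional on a split of 12/25 against 7/25, the rejection rate under no treatment effect is 5.8% and 6.9%.

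**5. Variance that severity alone could explain.** With 40% severe, R² = 0.4 × 0.6 × gap² / 18². This gives 0.02, 0.07, 0.17 and 0.30 for gaps of 5, 10, 15 and 20 points.

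**6. Power after adjustment.** Residual SD = 18 × √(1 − R²), 46 degrees of freedom, 25 per arm.

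| R² | Residual SD | Power at 15 | Power at 10 |
|---|---|---|---|
| none (48 df) | 18.0 | 82.3% | 48.6% |
| 0.02 | 17.8 | 83.0% | 49.3% |
| 0.05 | 17.5 | 84.1% | 50.5% |
| 0.10 | 17.1 | 86.0% | 52.7% |
| 0.20 | 16.1 | 89.7% | 57.5% |
| 0.30 | 15.1 | 93.2% | 63.3% |

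An R² of 0.20 is worth 1/(1 − 0.20) = 1.25 times the patients; an R² of 0.02 is worth 1.02 times.

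**The case against.** The strongest reply is that this is a condensed article. Covariates and the full case report form often sit in an analysis plan or full protocol that is not shown. The t-test appears only in the power paragraph, and powering on a t-test while analysing with covariates is common and conservative. The baseline list is headed as demographics and worded as inclusive, and clinical characteristics are promised separately, so fracture class may well be recorded. All of this stands as a limit on the point: the article shows that no adjustment is provided for and no class is listed, not that none will exist. What remains is that unstratified allocation is an explicit choice and that the one test named has no covariate.

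It is also right that omitting stratification is legitimate, that fracture site is already separated, and that the exclusions narrow the range of severity. They narrow it without making the remaining fractures alike, and a narrower range argues for the lower end of the assumed gaps.

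Two stronger readings are tempting, and the documents support neither.
- *An imbalance could not be corrected.* Eligibility already requires a judgement on fracture morphology and open-fracture grade, so related information exists at screening. A class could probably be read later from pre-operative images; that such images exist is an inference, since the article does not mention them.
- *Only people who know the arm could recover the class.* Definitive inclusion follows surgery, so pre-operative images pre-date allocation and a blinded reader could classify them afterwards. Recording the class beforehand is cleaner, but it is not the only route.

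**Conclusion.** The point holds as one of precision and robustness. The named analysis is valid: its type I error is about 5%, and its standard error already covers chance imbalance on average. It is less efficient than it could be, and it cannot respond to an imbalance once one is seen. A 20-percentage-point imbalance, with a probability of about 11–20% per group, would move the difference by 1–4 points. That is less than one standard error (5.1) and well below the 15-point target.

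The gain from adjustment ranges from negligible (83% and 49% power at 15 and 10 points if R² is 0.02) to useful (93% and 63% if R² is 0.30). With 40% severe, the top of that range needs a 20-point gap if severity acts alone; a 15-point gap gives R² of only 0.17, and age would have to supply the rest. The severe share, the gap, R² and the prognostic role of severity are all assumptions. The change is worthwhile because it is cheap, not because the plan is in error without it.

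**What to change.** - Record a fracture class for every patient before randomisation, using one established classification per fracture site read from existing pre-operative imaging, and add it to the baseline data.
- State that the primary analysis in each fracture group is a linear model with arm, age (continuous) and fracture class, with the class levels fixed in advance.
- Keep the unadjusted difference as a sensitivity analysis.
- If an unseen analysis plan or case report form already provides for this, a sentence in the protocol saying so is enough.

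The cost is one field on the case report form, a sentence of analysis wording, and two degrees of freedom among about 50 analysed patients per group (46 instead of 48, with the class in two levels). Stratifying the randomisation is optional at this size and not required for the gain. Patient management and sample size are unaffected.
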